#### Control Group

Participants randomized to the control condition will be given education about the benefits of physical activity and relaxation training but will receive no specific instructions about yoga practice for the 10-week intervention period.

### Outcome Measures

All outcome measures will be collected at baseline (week 0) and after the intervention period (week 11), as well as at 6 months follow-up. Qualified and experienced personnel, blinded to the group assignment of participants, will assess the primary and secondary outcomes within one testing session conducted at all three assessment timepoints.

#### Heart Rate Variability

The evaluation of HRV will be completed in a quiet and temperature controlled room in accordance with procedures developed by the *Task Force for Pacing and Electrophysiology *[30]. Participants will be advised to abstain from caffeinated food and beverages on the day of their assessments. Repeat assessments will be completed at precisely the same time of day. After 15 minutes of supine rest with a regular and calm breathing pattern, a continuous 10-minute ECG recording will be collected using an applanation tonometer interface with HRV software (Sphygmocor, AtCor Medical Pty, Sydney, Australia). The primary outcome of this study is the high frequency (HF) spectral power component of HRV (measured in absolute units; i.e. ms^2^). From the electrocardiographic recording, the following statistical and geometric time domain indices will be calculated from RR intervals: standard deviation of the NN intervals (SDNN), and the triangular index (TI). Frequency domain variables, including total, HF and low frequency (LF) power and LF:HF ratio will be derived from spectral analysis of successive R-R intervals. This technique separates the heart rate spectrum into its frequency components and provides quantitative estimates of sympathetic and vagal (parasympathetic) neural influences on the heart.

#### Physical Functioning

Upper-body and abdominal muscular endurance will be evaluated using the standardised push-up test and partial curl-up test, respectively, according to procedures outlined by the *American College of Sports Medicine *[27]. A modified version of the push-up test, allowing the participant to place their knees on the mat, will be used for participants who are unable to complete a single standard push-up [27]. Low back and hip flexibility will be evaluated *via *standardized sit and reach test using equipment and protocols outlined by the *American College of Sports Medicine *[27]. Low back and abdominal muscular endurance will be evaluated by means of an isometric, side-bridge test of muscular endurance [31]. This test demonstrates excellent test-retest reliability in adults (r = 0.99) [31]. Poor trunk muscle endurance has been implicated in the development of chronic low back pain [31].

#### Psychological Health Status

The *Medical Outcomes Trust Short-form 36 Health Status Questionnaire (SF36) *Version 1.0 [32] is a generic health status measure that assesses eight domains of quality of life. This instrument demonstrates a high degree of internal consistency and construct validity, has been designed for self-administration [32], and has been shown to be sensitive enough to detect changes over time in response to a yoga intervention [18,33]. The *State-Trait Anxiety Inventory *is a widely used and validated inventory that consists of two, twenty-item self-report scales for measuring state anxiety and trait anxiety as distinct and clearly defined psychological constructs in adults [34]. Job satisfaction and general work-related stress will be evaluated *via *global *Job Descriptive Index *and *Job in General Scale*, respectively [35]. Both scales have been validated for use in the general population, including office workers [35].

### Demographic and Health Status

Demographic and health status data will be extracted during the recruitment and screening process and baseline testing by means of standard questionnaires and assessments. Factors include height, body weight, resting systolic and diastolic blood pressure, waist circumference, demographic characteristics (i.e. age, gender, occupation, marital status, living arrangement, income, smoking history, alcohol intake, etc.), medication and supplement usage and dosage, adverse events related to medication/supplement intake, and any medical and surgical procedures received. Change of health status and physical activity in the experimental and control group during the 10-week intervention period will be documented by means of a structured questionnaire of open-ended questions that will be administered weekly *via *email. Acute illnesses, falls, changes in medication dosage and usage, adverse events related to yoga participation and visits to health care professionals will be documented in both the experimental and control group. Any participant experiencing an adverse event due to the yoga program will be referred to a qualified health care practitioner for appropriate management. All adverse events will be documented and reported.

### Statistical Analyses

Primary analysis will be via intention-to-treat with all patients included regardless of dropout or level of adherence. Missing data will be imputed according to the maximum likelihood expectation algorithm *via *the Statistical Package for the Social Sciences (IBM©, SPSS Version 19.0). Data will be presented as the mean ± standard deviation or median and range, as appropriate. Confidence intervals will be used to express group differences. Changes between groups will be determined by analysis of covariance of the post-treatment score controlling for the baseline score. Effect sizes and 95% confidence intervals will be calculated. A p value of < 0.05 will be considered indicative of statistical significance; clinical significance will be interpreted in light of the meaningfulness and magnitude of the adaptations observed.

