### Sample Size and Power Calculation

To our knowledge there are no published data on the effects of yoga training on resting HRV in a non-clinical population. However, it has been shown that yoga induces adaptations that are similar to those achieved with conventional exercise [25]. Therefore, data derived from an aerobic exercise intervention trial in an apparently healthy adult cohort [26] has been used to compute statistical power *a priori *using the non-commercial statistical power analysis program G*Power. The control group is expected to experience no change in the HF spectral power component from baseline (205.7 ± 205.7 ms^2^) while an experimental group is expected to increase this measure following the 10-week yoga intervention (568.0 ± 696.0 ms^2^). Setting an alpha level of 0.05, approximately 56 participants (28 per group) will provide 80% power to detect a statistically significant difference between groups. Recruitment will be inflated to 67 participants to enable a 20% participant attrition rate.

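### EM-filled outcomes are analysed by ANCOVA as if observed, so the primary 95% CI undercovers; whether the error rate rises or the effect shrinks depends on an unstated choice

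*Protocol article*

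**What the plan says.** The Statistical Analyses section of the protocol article fixes the primary analysis in linked steps.

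- Population: "Primary analysis will be via intention-to-treat with all patients included regardless of dropout or level of adherence".
- Missing values: "Missing data will be imputed according to the maximum likelihood expectation algorithm", carried out in SPSS 19.
- Test: ANCOVA with the post-intervention value as outcome and the baseline value as covariate, reported with 95% confidence intervals. "A p value of < 0.05 will be considered indicative of statistical significance".

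The section names no multiple imputation, pooling, bootstrap or other variance correction. It does not list the variables used in the imputation, so it is silent on whether treatment arm is one of them.

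The Sample Size and Power Calculation section shows how much missing data the design provides for: "Recruitment will be inflated to 67 participants to enable a 20% participant attrition rate".

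**The concern.** The EM algorithm estimates means and covariances well. Used to fill a data set, it replaces each missing value with its expected value given the other variables. Such values lie on the fitted regression with no scatter around it. An ordinary ANCOVA on the completed file then counts them as real observations. They add residual degrees of freedom and contribute nothing to the residual sum of squares. If arm was left out of the EM model, they also carry no treatment difference, because a yoga dropout and a control dropout with the same baseline receive the same value.

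The primary p value and confidence interval are at stake, since intention-to-treat brings every filled case into the primary test. In one case a null programme is declared effective too often. In the other a real effect is reported as smaller than it is, with an interval centred in the wrong place.

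**Working it through.** **Inputs from the protocol article**

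- Control HF power: "no change in the HF spectral power component from baseline (205.7 ± 205.7 ms^2"). Yoga: "expected to increase this measure following the 10-week yoga intervention (568.0 ± 696.0 ms^2").
- Alpha, size and power: "Setting an alpha level of 0.05, approximately 56 participants (28 per group) will provide 80% power".
- Recruitment of 67, with 20% attrition allowed for.

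**Inputs assumed here:** two-sided test; 34 and 33 per arm; missingness at random and only in the post score; imputation from baseline, with or without arm, and no auxiliary variables; baseline-post correlation 0.5 unless varied.

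**The plan's own figures**

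- Difference: 568.0 − 205.7 = 362.3 ms².
- Pooled SD: sqrt((205.7² + 696.0²)/2) = 513.2, so d = 362.3/513.2 = 0.706.
- The 67 is 56 × 1.2 = 67.2. Keeping 56 completers means losing 67 − 56 = 11 (16.4%). A full 20% loss leaves 67 × 0.8 = 53.6, so about 54 observed and 13 missing.
- A two-sided t test with these inputs gives power 0.737 at 28 per group, so the 56 is not reproduced. That is a separate matter; only d = 0.706 is used below.

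The article gives no standard error or false-positive rate under imputation, so there is no stated figure to reproduce for those.

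**Case A: arm in the EM model (or EM run by arm)**

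The point estimate has the same sampling spread as ANCOVA on the observed cases. Only the reported SE changes:

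SE ratio = sqrt((n_obs − 3)/(N − 3)) × sqrt(n_obs/N)

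The first factor is the residual mean square divided by too many degrees of freedom; the second is the inflated sample size.

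- 13 missing: sqrt(51/64) × sqrt(54/67) = 0.893 × 0.898 = 0.801. The 64-df critical value 1.998 becomes 1.998 × 0.801 = 1.601. On 51 df this has a two-sided tail of 11.6%.
- 11 missing: sqrt(53/64) × sqrt(56/67) = 0.910 × 0.914 = 0.832, giving 10.2%.

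Simulation, 20,000 trials per setting, no true effect:

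| Missing | SE ratio | False-positive rate | CI coverage |
|---|---|---|---|
| 5% | 0.95 | 6.1% | 93.9% |
| 10% | 0.88 | 8.4% | 91.6% |
| 11 of 67 | 0.83 | 10.2% | 89.8% |
| 13 of 67 | 0.80 | 11.6% | 88.4% |

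ANCOVA on the observed cases alone, at 13 missing, rejects in 5.0% and covers 95.1%. At 13 missing the EM result is stable: 11.5 to 11.8% for correlations from 0 to 0.8, 11.2% with lognormal data, and 11.6% with 30%/10% missing by arm. Adding a random residual to a single fill still gives 10.3%. With a true effect of 0.706 SD, the EM estimate is 0.707 and coverage is 88.5%.

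**Case B: arm left out**

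Filled values have the same expectation in both arms given baseline, so only observed cases carry the difference:

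expected estimate = d × n_obs/N = 0.706 × 54/67 = 0.569

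Simulation at 13 missing gives 0.566. With no true effect the rejection rate is 5.0% (range 4.8 to 5.2% with normal data, 4.3% with lognormal) and the SE ratio is about 1.0. At the planned effect, coverage is 89.3%, or 88.1% with 30%/10% missing by arm.

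**The case against.** The article is a condensed account and any SAP is not shown. It does not say that values are filled only once, and imputation variables and variance corrections are commonly left to a SAP. That is fair as far as the silence goes: not listing the variables is no fault in itself. But the article names a method and ties it to a test, and a single fill is the natural reading of an expectation-based algorithm with no pooling step. The criticism is of what is stated.

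A reader might infer more than the document supports:

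- **That the false-positive rate about doubles, full stop.** This holds only if arm enters the imputation. If it does not, type I error is held, and the bias runs against yoga. The text does not say which applies.
- **That the plan predicts 20% loss.** Twenty percent is an allowance. At 5% missing, even Case A gives only 6.1%.
- **That skewed HF power makes this worse.** SDs as large as the mean or larger suggest skewness, but lognormal data give 11.2% against 11.6%. Non-normality adds no demonstrated harm here.

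**Conclusion.** The point stands in conditional form. As written, EM-filled outcomes enter an ordinary ANCOVA with nothing to carry imputation uncertainty. At the planned effect and 13 of 67 missing, the nominal 95% interval covers about 88 to 89% in both cases, so that conclusion does not depend on the unstated choice.

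The mechanism does depend on it. With arm in the imputation model, the SE is about 20% too small and the two-sided false-positive rate is about 10% at 11 missing and about 12% at 13. Without arm, type I error is near 5%, but the estimate shrinks by about the missing share, from 0.706 to about 0.57 SD. All of this assumes post scores missing at random and no auxiliary variables, and it scales with the loss that actually occurs. Because it affects the primary result within the attrition that the design allows for, and is cheap to correct, it should be changed before the analysis.

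**What to change.** Keep the baseline-adjusted ANCOVA as the primary model. Replace the EM fill with multiple imputation that includes arm and baseline (or is run separately by arm), fit the ANCOVA in each completed data set, and pool with Rubin's rules. State the imputation variables. An acceptable alternative is a likelihood-based analysis of the observed data with its own standard errors and no filled values.

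The cost is a few sentences of analysis text and a little programming; recruitment, visits and measurements do not change. The interval will be wider. In the simulation at 13 missing and the planned effect, the SE from observed cases is 0.2375, against 0.1896 after an EM fill with arm (0.2375/0.1896 = 1.25) and 0.1932 without arm (0.2375/0.1932 = 1.23). The extra width is uncertainty that the present plan leaves out.

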## Methods and design

### Study Design

This is a parallel-arm randomized controlled trial that will compare the outcomes of participants assigned to the experimental treatment group (yoga) with those assigned to a no-treatment control group. The primary outcome of this study is the high frequency (HF) spectral power component of HRV (measured in absolute units; i.e. ms^2^), a measure of parasympathetic autonomic control. Secondary outcomes include additional frequency and time domains of HRV, and measures of physical functioning and psychological health status. The intervention period will be 10 weeks, and the assessment of primary and secondary outcome measures will be completed prior to and following the intervention period and at 6 months follow-up to determine the effect of intervention withdrawal. The University of Western Sydney Human Research Ethics committee has approved all research procedures.

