### Randomization

Participants will be randomized *via *computer-generated randomly permuted blocks [29] stratified by gender and age (< 50 years; > 50 years) into an experimental group and no-treatment control group. An investigator not involved in testing or delivery of the intervention will prepare the randomization assignments. Group assignment will be delivered to participants in sealed envelopes upon the completion of baseline testing.

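### Randomisation is stratified by gender and age group but the stated ANCOVA adjusts only for baseline, which costs some precision if either factor predicts the outcome beyond baseline

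*Protocol article*

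**What the plan says.** The Randomization section of the protocol article allocates participants in randomly permuted blocks, "stratified by gender and age (< 50 years; > 50 years) into an experimental group and no-treatment control group". That makes two factors with two levels each, so four strata. No block size is given.

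The Statistical Analyses section states the comparison as "analysis of covariance of the post-treatment score controlling for the baseline score". The baseline score is the only covariate named there, and no other section adds gender or age to a model. The sentence is not limited to one endpoint, so it also covers the secondary outcomes.

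On the endpoint, the Study Design section says: "The primary outcome of this study is the high frequency (HF) spectral power component of HRV". The sample size section says: "Setting an alpha level of 0.05, approximately 56 participants (28 per group) will provide 80% power". It rests on two group means and SDs and makes no stated allowance for covariates or strata.

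**The concern.** Permuted blocks within strata make the arms alike on gender and age group. If those factors are prognostic, that balance makes the treatment difference less variable from one hypothetical repetition of the trial to the next. A model that omits them still counts their variance as error, so its reported SE describes a more variable experiment than the one run. Confidence intervals come out too wide, the test rejects a true null less often than 5%, and power is given up.

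All of this depends on how far gender and age predict post-treatment HF power once baseline HF power is in the model. If they add nothing, the omission costs nothing.

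There is also a small defect in the strata themselves. As printed, one age group lies below 50 and the other above 50, so a participant aged exactly 50 belongs to neither, although the Participants section admits adults with no upper age limit.

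**Working it through.** **Inputs from the protocol article.** Control 205.7 ± 205.7 ms² and yoga 568.0 ± 696.0 ms²; 28 per group; alpha 0.05 with sidedness not stated (two-sided used below); four strata; ANCOVA on the baseline score alone.

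**Assumed, because the article gives no figure.** R², the share of residual variance after baseline that gender and age explain, is set at 0, 0.02, 0.05, 0.10 and 0.20. Block size is 4. Factor prevalences are 50% and 30% in one simulation, and 40% and 35% in a second. Baseline adjustment is given no benefit at first.

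**Step 1: effect size and the plan's own figure.**
- Difference: 568.0 − 205.7 = 362.3.
- Pooled SD: √((205.7² + 696.0²)/2) = 513.2.
- d = 362.3/513.2 = 0.706.
- A two-sided t-test at 28 per group then has 73.7% power (noncentral t), and 80% needs 33 per group. One-sided, 28 per group gives 83.2%, and 80% needs 26.

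The stated 28 for 80% is therefore not reproduced exactly. That is a separate matter; 73.7% serves here only as a starting point.

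**Step 2: expected size by algebra.** With the strata balanced, the true variance of the difference is about (1 − R²) times what the baseline-only model reports. The reported SE is then too large by the factor 1/√(1 − R²), and the actual type I error is about 2Φ(−1.96/√(1 − R²)).
- R² = 0.05: factor 1.026; 2Φ(−2.011) = 4.4%.
- R² = 0.10: factor 1.054; 2Φ(−2.066) = 3.9%.
- R² = 0.20: factor 1.118; 2Φ(−2.191) = 2.8%.

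**Step 3: simulation.** Each setting has 6,000 trials of 56 participants in stratified blocks of 4, each analysed with and without the two factors. Prevalences are 50% and 30%.

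| R² | Reported SE / true SD, baseline only | Type I error, baseline only | Power, baseline only | Power, with gender and age |
|---|---|---|---|---|
| 0 | 1.005 | 4.6% | 73.6% | 73.4% |
| 0.02 | 0.998 | 4.7% | 73.1% | 73.4% |
| 0.05 | 1.03 | 4.1% | 73.5% | 74.7% |
| 0.10 | 1.05 | 3.5% | 73.4% | 76.5% |
| 0.20 | 1.11 | 3.0% | 74.8% | 82.1% |

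The Monte Carlo standard error is about √(0.05 × 0.95/6000) = 0.3 points for a type I error near 5%, and √(0.75 × 0.25/6000) = 0.6 points for a power near 75%.

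The second simulation (prevalences 40% and 35%) agrees:
- R² = 0.10: mean SE 0.270 without the factors and 0.256 with them; type I error 3.9% without; power 72.9% against 76.4%.
- R² = 0.20: mean SE 0.269 against 0.241, a ratio of 1.12; type I error 3.1%; power 74.9% against 81.6%.

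**Step 4: cost if the factors do not matter.** Going from 53 to 51 error degrees of freedom at R² = 0 moves power from 73.7% to 73.6%.

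**Step 5: effect of the baseline covariate.** If baseline and post-treatment HF power correlate at ρ, the effect in residual SD units is 0.706/√(1 − ρ²). The article gives no ρ. Noncentral t at 28 per group gives:

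| ρ (assumed) | Baseline only | With factors, R² 0.05 | With factors, R² 0.10 |
|---|---|---|---|
| 0.38 | 80.1% | 82.0% | 84.0% |
| 0.5 | 85.0% | 86.7% | 88.4% |
| 0.6 | 90.0% | 91.4% | 92.7% |

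Absolute power rises with ρ, and the gain from adding the factors shrinks to between 1 and 4 points. This algebra slightly overstates the gain: at ρ = 0 and R² = 0.10 it gives 78.0 − 73.7 = 4.3 points, against about 3 in the simulation. It gives the baseline-only estimate no credit for the balance the strata already provide.

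**The case against.** The strongest reply is that the loss is hypothetical. No figure in the article shows that gender or age predicts post-treatment HF power beyond baseline, and baseline HF power may already absorb much of any stable age or gender difference. At R² of 0.05 or below the loss is about one point or less. This stands, and it is why the point is conditional.

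A second reply is that the simulated power levels give the baseline covariate no credit and use equal variances, whereas the protocol's SDs are 205.7 and 696.0. This also stands. The levels in Step 3 are not forecasts for the planned analysis; only the contrast between the two models is of use.

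A third is that this is a condensed article and that an unseen analysis plan may list further covariates. That softens the point without removing it: the article does state its covariate, and that covariate does not reflect the stratification.

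A reader might infer more than the documents support:
- **That the SE is certainly wrong and power certainly lost.** It is not certain, because R² is unknown and may be near zero.
- **That the trial is already short of its stated power, which would make this worse.** That rests on a two-sided test and on ignoring the baseline covariate. It belongs to the sample size question and is no evidence here.
- **That the gap at age 50 adds weight.** It is an allocation wording slip with no bearing on SE or power.

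**Conclusion.** The mismatch between design and model is plain in the text, and its direction is certain wherever the strata are prognostic: intervals too wide, a conservative test and some loss of power. The primary comparison remains valid, with an unbiased estimate and type I error at or below 5%, so this is a matter of efficiency.

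The size depends on an R² the article does not give. Under the assumptions listed it runs from nothing measurable (R² up to 0.02), through about 1 power point (0.05) and about 3 points with type I error of 3.5 to 3.9% (0.10), to about 7 points with type I error of about 3% (0.20). Adjustment costs about 0.1 point if the factors prove irrelevant, so the balance clearly favours including them. No calculation was made for the secondary outcomes, where the same reasoning applies but the size is unknown.

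**What to change.** In Statistical Analyses, prespecify gender and age as covariates beside the baseline score in the primary ANCOVA, and likewise in the secondary ANCOVAs. Age may enter as the two strata or as a continuous variable, but the choice should be fixed in advance. If the factors are to be left out, say why. Both are already recorded under Demographic and Health Status, so the cost is one line of model specification and two degrees of freedom.

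In Randomization, as a minor wording correction, make the age strata exhaustive, for example under 50 and 50 or over, so that every eligible participant has a stratum.
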